### Recruitment {15}

Subjects are recruited via the Internet (http://www.chictr.org.cn/index.aspx) and public places (such as the hospital bulletin board). The purpose is to publicize the study so that suitable patients can be enrolled in time. The BANBOO trial began to recruit in October 2021.

## Assignment of interventions: allocation

### Sequence generation {16a}

The randomized numbers were generated via computer by statistical investigators ([name] and [name]). This process was blinded to those researchers responsible for the conduct of the trial.

### Concealment mechanism {16b}

The randomized numbers were placed in opaque envelopes. The subject who decides to withdraw from the study will no longer be admitted to enter, and the subject number will not be assigned again.

### Implementation {16c}

Asymptomatic AAA is screened by CTA to determine the diameter of aortic aneurysm (30–50 mm). The maximal orthogonal AAA diameter on CTA is a measurement of infrarenal aortic diameter perpendicular to the lumen to avoid overestimation of the tortuous aorta. And then, the serum hs-CRP tests are performed in subjects with an eligible diameter of aortic aneurysm. Values of serum hs-CRP will be recorded at entry, 1 month, and 6 months. Immuno-turbidity is used to detect serum hs-CRP concentration. Eligible subjects are randomly assigned to the intervention arm (rivaroxaban) or control arm (aspirin) in a 1:1 ratio. [name] and [name] will enroll the participants to their allocation.

## Assignment of interventions: blinding

### Blinding (masking) {17a}

Statistical researchers will be blinded to the allocation.

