### Trial design {8}

The BANBOO trial is a prospective, single-center, open-label, randomized, controlled clinical trial conducted in the General Hospital of Northern Theatre Command of China. The protocol was designed to adhere to the recommendations of the Standard Protocol Items for Randomized Trials statement (SPIRIT) [23–25]. The research flowchart of the BANBOO trial is detailed in Fig. 2.

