### Outcomes {12}

The primary efficacy outcome is the level of serum hs-CRP at 6 months. The secondary outcomes include imaging examination (the maximal diameter of AAA, the maximal thickness of mural thrombus, and the length of aneurysm), major adverse cardiovascular and cerebrovascular events (MACCE, including AAA transformation, non-fatal myocardial infarction, acute congestive heart failure, stent thrombosis, ischemia-driven target vessel revascularization, vascular amputation, stroke, cardiovascular death, and all-cause death), other laboratory tests (troponin T, interleukin 6, D-dimer, and coagulation function). Blood will be taken at entry and 1 and 6 months to assess changes in circulatory indexes. CTA will be performed at entry and 6 months, depending on local ethics guidelines. The safety outcomes include bleeding events defined according to the Bleeding Academic Research Consortium criteria (BARC), liver function (determined by alanine aminotransferase), and renal function (determined based on the creatinine clearance rate). Detailed endpoints are listed in Additional file 1: Appendix A, and detailed definitions of endpoints are shown in Additional file 1: Appendix B. The results of the BANBOO trial will be interpreted based on all endpoints.

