There has been increasing evidence that aortic wall inflammation is the primary pathogenesis of AAA [5]. Studies showed that elevated hs-CRP positively correlates with AAA diameter size [36–38]. The concept that “lower is better” for hs-CRP influenced current guidelines [39, 40]. A study of 75 male patients and a study of 435 patients showed the serum hs-CRP as a marker of progression and expansion of AAA [41, 42]. One research suggested that hs-CRP is a valuable biomarker to assess the evolution of calcification [43]. Wang Y et al. evaluated the correlation between hs-CRP and AAA through systematic review including prospective studies, retrospective studies, and cohort studies. The results suggested that hs-CRP may possibly be used as a diagnostic biomarker in AAA patients with a medium to small aortic diameter but not in AAA patients with a large aortic diameter [44]. Hs-CRP could be a potential biomarker of AAA and a promising target to control the progression of AAA [8].

Studies showed a significant decrease in mean hs-CRP levels from baseline to the end of rivaroxaban treatment [10, 11]. The role of factor Xa in arterial thrombosis is considered due to its pro-inflammatory activity. The anti-inflammatory effects of rivaroxaban, a direct factor Xa inhibitor, may be particularly beneficial in inhibiting arterial thrombosis [12]. Rivaroxaban indirectly inhibits tissue factor-induced platelet aggregation by inhibiting thrombin production [13]. We hypothesize that rivaroxaban is a promising treatment strategy for small AAA with hs-CRP elevation. However, no clinical study of rivaroxaban in this field has been reported to date [45].

This study is a prospective, single-center, open-label, randomized controlled trial with a total sample size of 60 cases based on statistical calculation and the admission volume of patients with AAA in the research center. The study is blinded to the statistical investigator. The BANBOO trial is the first research to assess the efficacy and safety of rivaroxaban compared with aspirin in AAA patients with hs-CRP elevation.

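### The only stated blinding in this open-label trial is of the statisticians; CTA readers and event classifiers get none, and the blinding text is not reconciled with who generated the allocation list

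*Protocol article*

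**What the plan says.** All references are to the protocol article.

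- **Design** (Trial design {8}): "The BANBOO trial is a prospective, single-center, open-label, randomized, controlled clinical trial".
- **Blinding** (Blinding (masking) {17a}): the whole item reads "Statistical researchers will be blinded to the allocation". The Discussion repeats it: "The study is blinded to the statistical investigator".
- **List generation** (Sequence generation {16a}): "The randomized numbers were generated via computer by statistical investigators", followed by "This process was blinded to those researchers responsible for the conduct of the trial". Concealment mechanism {16b} adds "The randomized numbers were placed in opaque envelopes".
- **Outcomes** (Outcomes {12}): "The primary efficacy outcome is the level of serum hs-CRP at 6 months". Three CTA dimensions and MACCE are secondary, and BARC bleeding is a safety outcome. Implementation {16c} defines the diameter geometrically: "The maximal orthogonal AAA diameter on CTA is a measurement of infrarenal aortic diameter perpendicular to the lumen". It gives immuno-turbidity as the hs-CRP assay.
- **Analysis** (Statistical methods {20a}): continuous variables are compared by t-test or Mann–Whitney; baseline adjustment is not named. Current status and Data Availability place the analysis in a contract research organization's database.

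**The concern.** In an open-label trial the outcomes most in need of masked assessment are those that depend on a person's judgement. Here these are the measurement plane and endpoints chosen on a CTA, whether an event counts as AAA transformation or as ischemia-driven revascularization, and the grade of a bleed. The single safeguard stated goes to the statisticians instead.

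The gap falls on the outcomes closest to the trial's stated hypothesis. Background and rationale {6a} frames that hypothesis as control of AAA progression, Study setting {9} creates an imaging subgroup to study morphology, and Outcomes {12} says that interpretation will draw on all endpoints. A reader or classifier who knows the arm can shift these results, knowingly or not.

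The safeguard that is stated is also not fully explained, because the role described as blinded is the role that produced the randomization numbers.

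**Working it through.** **1. Who is masked, from the text.**

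| Role | What the article says |
|---|---|
| Patients and treating clinicians | Open-label |
| Researchers conducting the trial | List generation hidden from them; numbers in opaque envelopes |
| Statisticians | Blinded to allocation |
| CTA readers | Nothing stated |
| Those classifying MACCE and BARC bleeding | Nothing stated |

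The second row is allocation concealment. It protects assignment up to the moment of randomization and does nothing for outcome assessment afterwards.

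**2. List generation against blinding.** Sequence generation {16a} and the Discussion use the same job title; {17a} uses a near-synonym. No sentence separates the person who generates the list from the person who analyses, names a list custodian, or says that the analyst works from coded arms. The statements can all be true, but only under a separation that is not stated.

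**3. Which outcomes are exposed.** The hs-CRP primary outcome is an assay value with little reader judgement. CTA precedes randomization at entry, so only the 6-month reading can be influenced by knowledge of arm.

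**4. Illustrative size for diameter.** The article states no size for this risk, so there is no figure of its own to reproduce.

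Inputs:
- From the article: 30 per arm and 10% drop-out, so 30 × 0.90 = 27 evaluable per arm; two-sided level 0.05.
- Assumed, not in the article: SD of diameter 5 mm; baseline-to-6-month correlation r of 0.90 or 0.95 where baseline adjustment is used; a systematic reading difference b between arms of 0.5 or 1 mm; no true treatment effect.

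Formulas (normal approximation):
- Unadjusted SE = 5 × √(2/27) = 1.361 mm
- Adjusted SE = 5 × √(1 − r²) × √(2/27)
 - r = 0.90: 5 × 0.4359 × 0.2722 = 0.593 mm
 - r = 0.95: 5 × 0.3122 × 0.2722 = 0.425 mm
- False-positive rate = Φ(−1.96 + b/SE) + Φ(−1.96 − b/SE)

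| Analysis | SE (mm) | b = 0.5 mm: shift b/SE, rate | b = 1 mm: shift b/SE, rate |
|---|---|---|---|
| Unadjusted, as in {20a} | 1.361 | 0.37, 6.6% | 0.73, 11.4% |
| Adjusted, r = 0.90 | 0.593 | 0.84, 13.4% | 1.69, 39.2% |
| Adjusted, r = 0.95 | 0.425 | 1.18, 21.8% | 2.35, 65.3% |

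The more precise the analysis, the more a fixed reading bias matters. The first row belongs to the comparison that the article names; the other two apply only if a baseline-adjusted analysis is used.

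**The case against.** **Silence is not a statement.** No sentence says that CTA readers or classifiers know the arm. The article is condensed, and its endpoint definitions sit in an appendix that is not shown. This limits how firmly the point can be put. But {17a} is where assessor masking would be stated, it names one role only, and the design is open-label. Followed as written, the plan gives assessors no masking.

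**Same role, same people?** A reader might infer that the blinded statisticians are the individuals who made the list, so that the blinding claim is false. The documents do not support that. The titles differ slightly, no one is said to hold the list, the numbers went into envelopes, and the contract research organization's database is where analysis takes place. Generating a list also does not unblind an analyst who lacks the link to patients. What stands is that the statements need reconciling.

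**A threat to the primary result?** A reader might also infer that an unblinded analyst could push the primary type I error to about 11% by choosing among the permitted tests and imputations. Simulation under assumed distributions does give about 11% for the best of four choices. But group-mean imputation, allowed in {20c}, accounts for most of the excess: it gives about 8–9% with no choice at all. Picking the smaller two-sided p-value needs no arm labels either, so coded arms would not prevent it. That figure concerns the imputation rule and is no measure of the blinding gap.

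**The imaging figures are assumed.** This is fair. SD, correlation and bias are all assumptions, and the larger rates need an adjusted analysis that {20a} does not name. They show a range and are not an estimate.

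**Conclusion.** The point holds in limited form. The only blinding stated is of the statisticians, and no masking is given to those who produce the judgement-dependent secondary and safety outcomes. Separately, the statements on list generation and on blinding leave open whether the same people are meant, and should be reconciled.

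With SD 5 mm and 27 per arm assumed, a 0.5 mm systematic reading difference takes the false-positive rate for diameter from 5% to between about 7% (unadjusted) and 22% (adjusted, r = 0.95). A 1 mm difference takes it to between about 11% and 65%. Whether any such reading difference would occur, and in which direction, cannot be known from the article. No effect on the hs-CRP primary result is shown. The change is worth making because the exposed outcomes carry the progression hypothesis and the remedy is cheap; it does not call the whole trial into question.

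**What to change.** Amend Blinding (masking) {17a} as follows.

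1. Whoever already reads the CTAs measures the 6-month scans de-identified and without knowledge of arm.
2. MACCE and bleeding records are classified with study drug redacted where feasible.
3. The person who generated or holds the allocation list does not perform the analysis, and the analyst receives coded arms. List custody should not simply pass to the contract research organization, since its database is where the analysis takes place; that would blur the same separation.
4. Sequence generation {16a}, {17a} and the Discussion use one set of role names that makes this separation visible.

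**Cost.** Small handling time per scan and per event record, and a division of tasks to be written down. The sample size does not change. Redaction of bleeding records may be imperfect, because the clinical narrative can reveal the drug; the report should say so. The article describes the study as ongoing, and scans that have been kept can still be read masked.

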## Data collection, management, and analysis

### Data collection plan {18a}

CRF is used for data collection. Data is entered into the database, and all data need to be entered by two investigators. All data will be uploaded and updated on the Clinical Trial Management Public Platform (http://www.medresman.org.cn/ login.aspx).

### Plans to promote participant retention and complete follow-up {18b}

The investigator kept in touch with the subjects by telephone or WeChat and sent the results of each examination to the subjects to increase their compliance.

### Data management {19}

The data monitor was served by clinical trial experts who were not involved in this study. The monitor will check the data obtained from the trial and evaluate the arms of treatment. Monitors ensure that the trial team is conducting the study according to the protocol. All missing data needs to be accounted for and recorded in CRF. Investigators are required to sign off after completing the CRF.

### Confidentiality {27}

To protect the privacy of patients, truthfully inform the subject of the storage, use, and confidentiality measures of the subject’s personal information and do not disclose the subject’s personal information to a third party without authorization. Subjects provided written informed consent to allow the trial monitor to obtain and copy information in their medical records related to their participation in the study. As part of informed consent, the investigator will allow the trial monitor or regulatory authority to confidentially review any records that identify subjects in this study. This information can be shared with regulatory authorities; however, the trial monitor guarantees that personal and private information of the subjects will not be published elsewhere.

### Biological specimens {33}

The total amount of blood collected per patient at each visit was 18 ml. Blood samples for clinical laboratory tests are obtained by standard techniques and tested at local centers. The subject’s number and visit number should be pre-labeled on each specimen tube, at which time the researcher will add the patient’s personal information to the label. Biological specimens should be exhausted or disposed after statistical analysis.

### Additional consent provision for collection and use of participant data and biological specimens {26b}

The collection for a blood sample is informed on the ICF, and it is ensured that the results of each blood sample examination should be sent to the subject.

## Statistical considerations

### Statistical methods for primary and secondary outcomes {20a}

The primary endpoint analysis will be performed according to the intention-to-treat principle. The main aim of this study is to investigate whether rivaroxaban is superior to aspirin in reducing the level of serum hs-CRP in patients with AAA and hs-CRP elevation at 6 months. The null hypothesis (H0) for this analysis is that the level of the primary endpoint in the intervention arm is the same as that of the control arm, namely P0 = P1. The alternative hypothesis (H1) is that the levels of the primary endpoint in the two arms is not equal, namely P0 ≠ P1, and the superiority test is conducted at the 2-sided significance level of 0.05.

Continuous variables are presented as the mean ± standard deviation or the median with interquartile range and compared between two arms via *T*-test or Mann–Whitney *U* test. Categorical variables are presented as counts and percentages and compared between two arms via *χ*^2^ test. Kaplan–Meier curves and Log-rank tests are used to describe the cumulative incidences of MACCE and bleeding events. The differences in the risk of AAA between the two arms are estimated using a Cox proportional hazards model. A two-sided *P* < 0.05 is considered to be statistically significant. All statistical analyses are performed using the SAS (Version 9.3) software.

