### Inclusion and exclusion criteria {10}

The BANBOO study is designed to enroll 60 AAA subjects with hs-CRP elevation. Subjects aged 18 to 85 years, 30–50 mm in diameter of the aneurysm, and serum hs-CRP ≥ 2 mg/L are eligible for enrollment. Each enrolled subject should provide written informed consent before randomization. Complete inclusion and exclusion criteria are listed in Table 2 and Table 3.

**Table 2 Tab2:** Inclusion criteria

Inclusion criteria
1. 18–85 years old
2. AAA diagnosed by CTA; the maximal diameter of aneurysm is 30–50 mm
3. Serum hs-CRP ≥ 2 mg/L
4. Written informed consent

*AAA* abdominal aortic aneurysm, *CTA* computed tomography angioplasty, *hs-CRP* high-sensitivity C-reactive protein

**Table 3 Tab3:** Exclusion criteria

Exclusion criteria
1. ACS (unstable angina and acute myocardial infarction)
2. Dual antiplatelet therapy for stable CHD less than 6 months after PCI or ACS less than 1 year after PCI
3. Acute congestive heart failure or left ventricular ejection fraction ≤ 40%
4. Suffered from infectious diseases within 2 months before screening and infection has not been controlled more than 1 month
5. Active hepatitis, the elevation of alanine aminotransferase (ALT) value > 5 × the upper limit of normal
6. Severe renal failure (CrCl < 30 ml/min)
7. Life expectancy is less than 1 year
8. Any situation may interfere with the research process, such as dementia, paralysis, alcoholism, etc
9. Pregnancy or women during the lactation period
10. Suffered from hereditary connective tissue disease, such as Marfan’s syndrome, etc
11. Known allergies or intolerance to aspirin or rivaroxaban
12. AAA tends to rupture or has ruptured, and abdominal pain aggravates
13. Major surgery within 1 month
14. Active stage of severe peptic ulcer or previous bleeding events (including retinal or vitreous hemorrhage, urinary tract hemorrhage, etc.) within 6 months
15. Have participated in other ongoing clinical studies
16. Refuse to provide a written informed consent
17. Other unsuitable conditions adjudicated by investigators

*ACS* acute coronary syndrome, *CHD* coronary heart disease, *PCI* percutaneous coronary intervention, *CrCl* creatinine clearance rate, CrCl = body weight(kg) × (140-age)/[0.818 × CREA(μmol/L)][serum creatinine (CREA) is tested by enzymatic method. Female: above data results × 0.85]

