### Sample size calculation {14}

Power calculations are based on a superiority comparison of the primary endpoint. Assuming the level of serum hs-CRP in the aspirin arm (control) is 4.79 ± 3.2 mg/L at 6 months, and taking the drop-out rate is 10%, 30 patients in each arm (60 in total) are planned to be enrolled and randomly assigned in a 1:1 ratio, to provide 90% power to detect a 2.54 mg/L absolute value reduction in rivaroxaban arm (intervention) in comparison with that in aspirin group with a 2-sided type I error of 0.05.

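### The 6-month hs-CRP comparison is an unadjusted T-test or Mann–Whitney test, with neither named as primary, and leaves every patient's baseline hs-CRP unused

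*Protocol article*

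**What the plan says.** Outcomes {12} defines the endpoint as a level, not a change: "The primary efficacy outcome is the level of serum hs-CRP at 6 months".

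Statistical methods {20a} puts the primary analysis under intention to treat and tests for a difference between arms at the two-sided 0.05 level. Its only method for a continuous variable is one general sentence: "median with interquartile range and compared between two arms via *T*-test or Mann–Whitney *U* test". It gives no covariate, transformation or rule for choosing between the tests, and does not say which one decides the primary hypothesis. The sentence covers continuous variables in general; it reaches the primary endpoint because no other method is given for it.

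Baseline values exist for everyone. Implementation {16c} says: "Values of serum hs-CRP will be recorded at entry, 1 month, and 6 months". Table 1 schedules the same three draws. Under the eligibility criteria {10}, only subjects with "serum hs-CRP ≥ 2 mg/L are eligible for enrollment", so nobody can be randomized without a baseline measurement of the endpoint itself.

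The sample size {14} is built on raw means: "Assuming the level of serum hs-CRP in the aspirin arm (control) is 4.79 ± 3.2 mg/L at 6 months", and a design "to provide 90% power to detect a 2.54 mg/L absolute value reduction in rivaroxaban arm", "with a 2-sided type I error of 0.05".

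**The concern.** A two-sample test of follow-up values ignores whatever each patient's baseline predicts about the outcome. With 30 per arm that matters in two ways.

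- **Precision.** The variation explained by baseline stays in the error term.
- **Chance imbalance.** If one arm starts with higher hs-CRP, part of that carries through to month 6 and is read as a treatment effect.

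Two further points concern the choice of test. The T-test on raw means sits poorly with the plan's own mean and SD for a marker that cannot be negative. The Mann–Whitney test copes with skewness but gives no mg/L difference to set against the 2.54 mg/L used for the sample size. With both named and neither primary, the article does not say which quantity the trial will report as its main result.

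**Working it through.** **Inputs from the article.** Control mean 4.79 and SD 3.2 mg/L; difference 2.54, so an implied rivaroxaban mean of 4.79 − 2.54 = 2.25; two-sided alpha 0.05; 30 per arm; 10% drop-out, so 30 × 0.9 = 27 completers per arm.

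**Assumed, because the article does not give them.** The same SD of 3.2 in both arms, unless stated otherwise; rho, the correlation between baseline and 6-month hs-CRP.

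**1. The plan's own figure.** n per arm = 2 × [3.2 × (1.96 + 1.28)/2.54]² = 33.4, so 34, and 34/0.9 = 37.8, so 38 with drop-out. The stated 30 is not reproduced under a common SD. That is a separate matter; here it only means there is no spare precision to give away under that assumption.

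**2. Power of the unadjusted test.** Noncentrality = (2.54/3.2) × √(27/2) = 2.92 on 52 degrees of freedom. Power is 82%.

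**3. Power with baseline adjustment.** The residual SD is 3.2 × √(1 − rho²), with 27 per arm.

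| rho (assumed) | residual SD | power |
|---|---|---|
| 0 (unadjusted) | 3.20 | 82% |
| 0.2 | 3.14 | 83% |
| 0.3 | 3.05 | 85% |
| 0.4 | 2.93 | 88% |
| 0.5 | 2.77 | 91% |
| 0.6 | 2.56 | 95% |

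**4. Chance imbalance.** With 30 per arm the difference in baseline means has standard error √(2/30) = 0.26 SD. An imbalance of 0.5 SD or more (0.5/0.258 = 1.94 standard errors) therefore occurs about once in 20 trials. Unadjusted, it shifts the expected 6-month difference by rho × 0.5 × 3.2: 0.48 mg/L at rho 0.3 and 0.80 mg/L at rho 0.5, against a target of 2.54.

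**5. Fit of the raw scale.** Normal probability below zero: Φ(−4.79/3.2) = Φ(−1.50) = 6.7% in controls, and Φ(−2.25/3.2) = Φ(−0.70) = 24% in the rivaroxaban arm if the SD is common. A log-normal distribution with the same coefficient of variation (3.2/4.79 = 0.67) has log-SD √ln(1 + 0.67²) = 0.61 and skewness 2.3.

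**6. Simulation on that log-normal model, 27 per arm, SD proportional to the mean.**

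Null, rho 0.5, 10,000 runs. Rejection rates:
- raw T-test 4.8%
- Mann–Whitney 4.8%
- log-scale ANCOVA 4.8%
- smaller of the T-test and Mann–Whitney p-values 6.7%

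Power, 3,000 runs per row (simulation error up to about 0.7 percentage points):

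| true reduction | rho | raw T-test | Mann–Whitney | log ANCOVA |
|---|---|---|---|---|
| 53% (planned, 2.54/4.79) | 0.3 | 97.5% | 98.9% | 99.5% |
| 53% (planned) | 0.5 | 98.0% | 98.9% | 99.9% |
| 40% (assumed) | 0.3 | 81% | 84% | 89% |
| 40% (assumed) | 0.5 | 78% | 82% | 93% |

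**The case against.** The strongest reply is that nothing stated is invalid. Both tests hold their size on skewed data, and Mann–Whitney is unaffected by a log transformation. A reader might infer that the plan mishandles a skewed marker. That goes too far: the poor fit concerns only the raw-mean T-test, and there it costs efficiency rather than validity.

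A reader might also infer that the test will be picked after seeing the results. The text does not say so. One general sentence in a condensed article may be completed in an analysis plan not shown here, and {17a} blinds the statistical researchers to allocation. The 6.7% error rate applies only if the smaller p-value were always the one reported.

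Nor does a single extreme value readily manufacture a positive finding. A value of 60 mg/L in place of an average one moves a 27-patient mean by (60 − 4.79)/27 = 2.0 mg/L, but it also inflates the SD. In a null simulation of 4,000 runs, forcing one such value cut T-test rejections from 4.3% to 0.2% and left Mann–Whitney at 4.4%. The harm is lost T-test power, which the other named test largely avoids.

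Two objections limit the size of the gain, and both stand. Rho is not in the article, and selecting patients at hs-CRP ≥ 2 mg/L narrows the baseline range, which tends to lower the correlation. In one illustration with assumed log-normal inputs, 0.5 before selection became about 0.30 to 0.37. Also, the 40% reduction is not the planned effect; at the planned 53% with a proportional SD, the choice of method costs almost nothing.

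What the reply does not remove is the core. The article states the tests, and neither uses baseline. This is a choice made in the text, not a detail left out.

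**Conclusion.** The point holds as one of efficiency and clarity. The stated analysis leaves unused a baseline measurement available on every randomized patient and does not say which of two tests is primary. Under a common SD of 3.2 and 27 completers per arm, adjustment raises power from 82% to between 83% and 95% for rho from 0.2 to 0.6, with the lower part of that range the more cautious expectation given the entry cut-off. On the log-normal model at a 40% reduction, log-scale ANCOVA gains about 5 to 12 percentage points over Mann–Whitney and about 8 to 15 over the raw T-test, for rho of 0.3 to 0.5. At the planned 53% reduction with a proportional SD, all methods reach about 98% or more. The change therefore matters mainly if the true effect is smaller than planned or the SD does not shrink with the mean. It should be made, but the trial's validity does not hang on it.

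**What to change.** In {20a}, replace the general sentence, for the primary endpoint only, with one named analysis: ANCOVA of log(hs-CRP) at 6 months on treatment arm and log baseline hs-CRP, in the intention-to-treat population, reported as the ratio of geometric means (rivaroxaban to aspirin) with 95% CI and a two-sided test at 0.05. Keep the Mann–Whitney test as a sensitivity analysis. Recruitment began in October 2021, so date the amendment and make it before hs-CRP is examined by arm.

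The cost is a change of text; the data are already scheduled and the case report form stays as it is. The one small downside is that the effect becomes a ratio and not the mg/L difference behind the sample size. A back-transformed or raw mean difference can be reported alongside, so that the result can still be set against 2.54 mg/L.
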